### Interventions

A total of 12 sessions of electrostimulation treatment will be performed, twice a week, on non-consecutive days. In order to minimize any effects of physiological filling of the bladder due to the applied technique, as part of the intervention procedure, the participants will be required to try to empty the bladder before each session, even if they report the absence of the need to urinate. In order to verify the post-void residual volume, an ultrasound (US) examination will be performed using a GE Healthcare Venue 40® ultrasound (probe 4C) (GE Healthcare, Chicago, IL, USA). The participant will remain lying on a bed in the supine position, the infra-abdominal region will be cleaned with 70% alcohol, with the ultrasound conducting head positioned vertically on the lower abdomen to locate the bladder and perform the necessary measurements. The following equation will be used to measure bladder volume: Volume = Length × Width × Height × 0.52, this being an easy, fast, and reliable method [34]. The post-void residual volume will be considered as values of up to 50 ml [35]. As a way of controlling the volume of urine, the same US procedure will be performed after the intervention (treatment). This procedure will be performed pre- and post-intervention treatment in all sessions of electrostimulation.

The electrical stimulation techniques used will be TTNS, PTES, and placebo electrostimulation. During the treatment all sessions will be conducted according to the following flowchart (Fig. 1) for the three groups.

For the description of the correct way to report electrostimulation, the recommendations of Barbosa et al. [36] will be followed. For the treatment with electrostimulation, a balanced asymmetric pulsed current of constant voltage will be used, in transcutaneous application mode, with a Tens Vif 993 Four four-channel device (Quark®, Brazil). The company that produces the device has the proper credentials in the Registry with the National Health Surveillance Agency (ANVISA) under registration number 80079190023. The company meets the standards NBR ISO 9001, NBR ISO 13485 and RDC 59 (Good Practice Guidelines) and has the authorization of the Brazilian Health Ministry. The electrodes will be surface (silicone rubber and carbonate), brand Quark®, with dimensions of 5 cm by 3 cm, coupled with conductive gel and fixed on the skin of the volunteer with micropore tape. The positioning of electrodes and adopted parameters can be observed in Fig. 2.

**Fig. 2 Fig2:**
[figure not shown]
Layout of the positioning of the electrodes and parameters for each group

The same parameters will be used in both groups, PTES and TTNS: frequency 10 Hz (Hertz), pulse duration 200 μs (microseconds), during 20 minutes [25, 37]. Every 3 minutes the participant will be asked about the sensation and, if necessary, the intensity will be increased, always maintaining a strong but not painful sensation.

For the positioning for the TTNS technique, the volunteer will be placed in the supine position on the bed with knee in semi-flexion and head resting on a pillow. The electrodes will be positioned one immediately posterior to the medial malleolus of the ankle and another approximately 10 cm above this, fixed with micropore tape. In order to ensure that the electrodes stimulate the tibial nerve, a current with a frequency of 1 Hz will be applied first, with a gradual increase in intensity to verify a rhythmic flexion movement of the hallux. After confirming the correct positioning, the device will be switched off and when the device is switched on again, the above parameters will be used and the initial intensity adjusted according to the sensitivity of the participant, below the motor threshold [37].

For the PTES technique, the participant will be positioned in left lateral decubitus on the bed, with 90° hip flexion, knee in semi-flexion, erect trunk, and head resting on a pillow. The electrodes will be placed side by side symmetrically, with conductive gel, approximately four centimeters apart, at the level of the third sacral vertebrae (S3). For the exact positioning of the electrodes, the anatomic reference bone, posterior superior iliac spine (PSIS) (which corresponds to the level of the second sacral vertebrae [S2]) will first be located, after which the electrodes will be positioned using the measurement of the participant’s two-finger distance below the PSIS.

Regarding the placebo group, the participant will be positioned in left lateral decubitus on the bed with 90° hip flexion, knee in semi-flexion, erect trunk, and head resting on a pillow. The electrodes will be placed concomitantly at three sites: the tibial and parasacral positionings (mentioned above), and the scapula, with an inter-electrode distance of approximately 4 cm; however, only the channel to the scapular region will be activated, the rest remaining inactive (adapted from Lordêlo et al. [25]). It should be noted that the region of the scapula is not part of the nerve path referring to the detrusor, or pelvic floor, thus designated as no effect for treatment of voiding dysfunctions. The parameters used will be a frequency of 100 Hz, pulse duration 100 μs, and time of 20 minutes. This configuration is known as conventional transcutaneous electrical nerve stimulation [38], and commonly used for non-invasive and non-pharmacological treatment of pain, free of side effects [39, 40]. Monitoring of intensity will be the same as for the electrostimulation protocols described above.

### Blinding

Given the nature of the researcher, it is not possible to blind participants to electrostimulation. However, the participants are blinded to the hypothesis of the study and to the group in which they are allocated. The principal investigator, due to the nature of the intervention, cannot be blinded in relation to the groups, but will be blinded on the outcomes of the evaluations made by the assessor blinded to the participants’ allocation.

### Measurement of results, primary and secondary outcomes

The outcome measures will be evaluated in several stages: at the beginning before the randomization (Anamnesis record, OAB-V8, ICIQ-OAB, KHQ, 24 h-VD), during the 12 sessions (Session Monitoring Card), in the 6th and 12th sessions (OAB-V8, ICIQ-OAB, KHQ, 24 h-VD), and 30 days after the end of treatment (Follow-up Monitoring Card, OAB-V8, ICIQ-OAB) (Table 1). The primary outcome of the study is urgency, measured by the OAB-V8. This was chosen as it is a validated instrument for Portuguese, with criteria defined for identification of urgency, easy to apply, objective, with robust results. It is used both as a screening tool and to raise self-identification awareness of the participant. In addition, as a primary outcome, the number of episodes of urgency will be observed (obtained in the Session Monitoring and Follow-up sheets). As secondary outcomes: voiding habits (number of diurnal urinations (Session Monitoring and Follow-up sheets and ICQ-OAB), use of absorbent pads (KHQ), urinary incontinence (number of episodes of urinary loss Session Monitoring and Follow-up sheets and ICIQ-OAB, severity of UI (ICIQ-OAB)) and quality of life (KHQ and ICIQ-OAB).

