### Statistical analysis plan

The statistical analysis will be performed by a statistician blind to the allocation of the groups and without involvement in the research. The software SPSS 16.0 and R 3.5.1 will be used for the analysis of data (IBM SPSS Statistics, Armonk, NY, USA). The level of significance will be set at 5%. The normality of the residues will be verified by the Shapiro-Wilk test.

The comparison of urgency, voiding habits, UI, and quality of life between groups (TTNS, PTES, and placebo) and between stages (pretreatment, 6th and 12th evaluation, follow-up), as well as the interactions between these will be performed by means of ANOVA of mixed models considering group and time factors for repeated measures if the residuals present normality with post hoc contrasts (treated versus placebo group, TTNS versus PTES).

The first statistical procedure will be to verify, in general and at each evaluation stage (pretreatment, 6th and 12th evaluation, follow-up) if the urgency, voiding habits, UI, and quality of life differ in the TTNS and PTES groups compared to the placebo group. The null hypothesis is that in both the TTNS group and the PTES group, urgency, urinary habits, urinary incontinence, and quality of life will be the same as the placebo group. The alternative hypothesis is that the TTNS and PTES groups will differ from the placebo group.

The second statistical procedure has the intention of verifying whether, in general and at each stage of evaluation (pretreatment, 6th and 12th evaluation, follow-up), urgency, voiding habits, UI, and quality of life differ between the TTNS group and the PTES group. The null hypothesis is that in both the TTNS group and the PTES group the behavior is the same. The alternative hypothesis is that there is a difference in behavior between these two groups.

The third statistical procedure aims to verify if there is alteration in the urgency, voiding habits, UI, and quality of life throughout the four stages of study evaluation (pretreatment, 6th and 12th evaluation, follow-up) within each of the groups. The null hypothesis is that the behavior is the same throughout the stages in each group. The alternative hypothesis is that there is a difference in the stages in each group.

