In the interview, the anamnesis record will be applied, which generates qualitative variables that will be presented as frequencies and percentages, and quantitative variables that will be presented as minimum value, maximum value, mean, median, standard deviation, coefficient of variation, and asymmetry coefficient. The ICIQ-OAB, KHQ, OAB-V8, and 24 h-VD will be applied, which will result in quantitative scales that will be presented as minimum value, maximum value, mean, median, standard deviation, coefficient of variation, and asymmetry coefficient.In the 6th and 12th sessions, the ICIQ-OAB, KHQ, OAB-V8, and 24 h-VD will be applied, which will result in quantitative scales that will be presented as minimum value, maximum value, mean, median, standard deviation, coefficient of variation, and coefficient of asymmetry.In the follow-up, the ICIQ-OAB, OAB-V8 and Follow-up Monitoring Card will be applied, which will result in quantitative scales that will be presented as minimum value, maximum value, mean, median, standard deviation, coefficient of variation, and coefficient of asymmetry.In all sessions during the treatment, a Session Monitoring Card will be applied that will generate quantitative variables that will be presented as minimum value, maximum value, mean, median, standard deviation, coefficient of variation, and coefficient of asymmetry.At the end of the treatment, the ANOVA for repeated measurements will be applied to verify the effects of the three groups and the three stages (pretreatment, 6th and 12th evaluation), and the interactions between them in the KHQ, ICIQ-OAB, OAB- V8, and 24 h-VD, if the residues present normality. If the residues do not present normality, a non-parametric test will be applied.At the end of the sessions and follow-up, the ANOVA for repeated measures will be applied to verify the effects of the three groups and the four stages, and the interactions between them in the OAB-V8, ICIQ-OAB, and Monitoring Cards (sessions and follow-up), if the residues present normality. If the residues do not present normality, a non-parametric test will be applied.At the end of the sessions and the follow-up, the ANOVA for repeated measurements will be applied to verify the effects of the 13 stages (12 sessions and follow-up) of the Monitoring Cards (sessions and follow-up), if the residues present normality. If the residues do not present normality, a non-parametric test will be applied.

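### Two unranked primary outcomes, one 5% level and comparisons at every stage leave the active-versus-placebo claim without error control; the joint null also does not say which technique works

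*Protocol article*

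**What the plan says.** **Outcomes.** Under Measurement of results, primary and secondary outcomes: "The primary outcome of the study is urgency, measured by the OAB-V8". The same paragraph goes on: "In addition, as a primary outcome, the number of episodes of urgency will be observed", with the counts taken from the session and follow-up monitoring sheets.

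**Level and contrasts.** The Statistical analysis plan section states one level ("The level of significance will be set at 5" per cent). It plans a mixed-model ANOVA with "post hoc contrasts (treated versus placebo group, TTNS versus PTES"). The first procedure asks whether the active arms differ from placebo "in general and at each evaluation stage (pretreatment, 6th and 12th evaluation, follow-up").

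**Null.** The first null sets both active arms equal to placebo on all outcomes at once: "The null hypothesis is that in both the TTNS group and the PTES group, urgency, urinary habits, urinary incontinence, and quality of life". The alternative is that the TTNS and PTES groups differ from placebo.

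**Models.** The detailed list analyses OAB-V8 at the end of treatment for "the effects of the three groups and the three stages (pretreatment, 6th and 12th evaluation"), and again over four stages once follow-up is complete.

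**Timing.** Trial design gives separate dates for the primary-analysis data (December 2019) and the follow-up data (February 2020). The Abstract and Sample size sections base the urgency comparison and the calculation on four stages, follow-up included.

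**The concern.** A confirmatory trial needs to fix which result decides the primary question. Here a difference on either outcome, for either technique, at the 6th session, the 12th session or follow-up could be put forward as the primary finding, each tested at 5%. The Discussion points the same way: it looks for the effect at the 6th and 12th sessions or one month later, on several instruments. The Trial design dates suggest that the primary analysis comes before follow-up, but they do not choose between the 6th and 12th sessions, and the four-stage sample size does not fit them.

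The joint null is a separate matter. The Discussion hopes to support recommendations on TTNS and PTES, which needs a conclusion for each. Rejecting a null that covers both arms shows only that some difference exists.

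**Working it through.** **1. The plan's own figure.** Inputs from Sample size: 3 groups, 4 stages, effect size f = 0.15, alpha 5%, power 90%. Assumed, because not given: correlation between stages 0.5 and sphericity (the software's defaults). For the group-by-time interaction:

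- noncentrality = f² × N × m / (1 − rho) = 0.0225 × 99 × 4 / 0.5 = 17.82
- degrees of freedom: (3 − 1)(4 − 1) = 6 and (99 − 3)(4 − 1) = 288
- power = 0.9003

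So 99 is right for one interaction test on one outcome at 5%. If the 5% were split equally between two primary outcomes, the same test would have 84.2% power at 99 and would need 114 participants (38 per group). The sizing does not cover the second primary outcome.

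**2. Which tests count.** A pretreatment difference is not evidence of effect, and TTNS versus PTES says nothing about beating placebo. That leaves 2 outcomes × 3 post-baseline stages × 2 active-versus-placebo contrasts = 12 tests. If they were independent, the chance of at least one false positive would be 1 − 0.95^12 = 46%. They are correlated, so the true figure is lower.

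**3. Simulation with no true effect.** 33 per arm, 20,000 trials per setting, pooled-variance t contrasts, two-sided 5%. The correlations are assumptions. Columns give the correlation between stages / between outcomes.

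| At least one false active-versus-placebo result | 0.5 / 0.3 | 0.5 / 0.5 | 0.7 / 0.5 | 0.7 / 0.7 | 0.8 / 0.8 |
|---|---|---|---|---|---|
| 1 outcome, 1 stage, 2 contrasts | 9.2% | 8.9% | 9.2% | 9.2% | 8.9% |
| 2 outcomes, 1 stage, 2 contrasts | 17.1% | 16.0% | 16.4% | 14.8% | 13.8% |
| 1 outcome, 3 stages, 2 contrasts | 22.1% | 21.8% | 19.0% | 19.0% | 17.2% |
| 2 outcomes, 3 stages, 2 contrasts | 38.2% | 36.9% | 32.4% | 30.1% | 25.2% |
| the same, favouring an active arm only | 19.5% | 18.7% | 16.3% | 15.7% | 12.8% |
| 2 outcomes, 3 stages, one pooled treated-versus-placebo contrast | 23.2% | 22.0% | 19.3% | 17.7% | 14.8% |
| 2 outcomes, 3 stages, 2 contrasts, only after a significant group or interaction F for that outcome | 12.8% | 12.0% | 11.2% | 10.6% | 9.1% |

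The benchmark for the favourable-only row is 2.5% per two-sided test, not 5%. A separate simulation over the same range of correlations put the last row at 10-14%.

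**4. OAB-V8 analysed twice.** The interaction test over four stages alone rejects in about 5% of null trials. Allowing either the three-stage or the four-stage test to count gives 6.8-7.1%.

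**5. After the change proposed below.** One outcome at one stage, two contrasts, the smaller p-value tested at 2.5%: familywise error 4.6-4.8%.

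**The case against.** **Stronger readings that the document does not support.** A reader might count all three pairwise contrasts at all four stages for both outcomes, 24 tests in all. That gives about 36-56% and could be called the chance of a false claim of efficacy. It is not. The count includes pretreatment and TTNS-versus-PTES comparisons, and Table 1 has no pretreatment entry for the session card that supplies the episode counts. A reader might also infer that the joint null is what raises the error. A joint null tested once keeps its 5%; the excess comes from separate contrasts at 5% each.

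**Post hoc may imply a gate.** Contrasts are often read only after a significant overall test, which would bring the figure to 9-14%. This is fair, but the article states no such gate, and even then the error is about double the nominal level or more.

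**Treated versus placebo may mean one pooled contrast.** This is possible and gives 15-23%. The first procedure, which names both active groups against placebo, fits two contrasts at least as well.

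**A primary time is implied.** The Trial design dates do separate the primary analysis from follow-up. That narrows the choice without settling it.

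**A fuller analysis plan may adjust the contrasts.** It may, and the absence of an adjustment method is not the point. What this article itself fixes is two unranked primary outcomes, one level, comparisons at each stage and a sample size for one test.

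**Conclusion.** The point holds. As written, the chance of at least one false active-versus-placebo difference on a primary outcome is about 25-38%, or about 13-20% counting only differences that favour an active arm. It is 15-23% with one pooled contrast and about 9-14% if an unstated overall gate applies. All of these rest on assumed correlations of 0.5-0.8 between stages and 0.3-0.8 between outcomes, which the document does not give. Every reading tried with both primary outcomes exceeds its benchmark of 5% (2.5% per test for favourable results), so the direction is firm even though the exact size is not.

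Two parts are smaller or different in kind. Running OAB-V8 over both three and four stages adds little (about 5% to 7%). The joint null is a fault of interpretation: rejecting it does not identify the technique that works. The sample size of 99 is correct for its own single test.

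**What to change.** Before any analysis (Trial status says none has been done), change the wording as follows:

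- Name one primary outcome at one stage. OAB-V8 at the 12th session is one choice that fits the Trial design dates; a stated ranking or alpha split between the two outcomes would also work.
- State two separate null hypotheses, TTNS versus placebo and PTES versus placebo, and test them with Holm's procedure at a total of 5%.
- Make urgency episodes a key secondary outcome.
- Fit one OAB-V8 model that includes follow-up, in place of the three-stage and four-stage versions.
- Keep TTNS versus PTES as a pre-specified secondary comparison with a confidence interval, since the hypothesis in the Introduction is that urgency falls similarly after both.
- Report other stages as supportive, with confidence intervals.

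**Cost.** No new data are needed, and all planned measurements stay in use. Each contrast loses a little power. A contrast with 90% power at 5% has 1.960 + 1.282 = 3.242 standard errors in hand; at 2.5% the critical value is 2.241, which leaves 1.000 and a power of about 84%. Holm falls between 84% and 90%, because the second test regains the full 5% once the first is rejected. Baseline adjustment may win some of this back, but how much depends on a correlation that the document does not state, so the plan should not claim it.

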## Introduction

The International Continence Society defines urinary incontinence (UI) as any involuntary loss of urine [1, 2] and is classified as urinary stress incontinence, urgency urinary incontinence (UUI), and mixed urinary incontinence [3]. UUI occurs due to a contraction of the detrusor muscle at the bladder filling stage, with urine loss, accompanied or preceded by urgency [4]. An overactive bladder (OAB) occurs when there are symptoms of urgency with or without UI, usually polyuria and nocturia [4, 5].

UI is a public health problem, affecting, above all, older people [6] and women [7]. With regard to UUI, it is associated with a significant and clinically important decrease in health-related quality of life (QoL) [8, 9]. The prevalence of UUI is 1.8–30.5% in European populations, 1.7–36.4% in the United States, and 1.5–15.2% in Asian populations [10].

Electrical stimulation is used as a resource for UUI treatment in the physiotherapist’s clinical practice [11, 12]. Transcutaneous tibial nerve stimulation (TTNS) aims to facilitate inhibition of the detrusor muscle [13] by means of electrostimulation in the path of the tibial nerve [14]. The tibial nerve is a mixed nerve [15], that originates in the L5-S3 nerve roots, which are the same roots that innervate the parasympathetic pathway of the bladder (S2-S4) [14, 16], thus, it is suggested that direct stimulation of the tibial nerve could inhibit the S2-S3 afferents, thereby decreasing detrusor hyperactivity. This is a simple, non-invasive, well-tolerated technique considered conservative and effective therapy for patients with UUI [17] and OAB [11].

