### Participants and settings

The trial is underway in the Laboratory of Research in Women’s Health (LAMU), in the Physiotherapy Department of the Federal University of São Carlos (UFSCar), in São Carlos, Brazil. Participants are being invited through informal invitation in social groups, and the research will also be disseminated through the internet on the UFSCar dissemination site and on social networks and leaflets. The objectives of the study will be explained by the researcher, who will clarify all doubts and questions in relation to the research, and individuals who agree to participate will sign the ICT. After selection of the participants, scheduling will take place for evaluations of eligibility of the sample and, later, for the start of treatment.

The inclusion criteria considered will be: women over 18 years of age; with urgency, self-reported and confirmed by a score greater than or equal to 8 on the Overactive Bladder – Validated 8-Question Awareness Tool (OAB-V8) [28] questionnaire. The exclusion criteria will be: stress urinary incontinence with no urgency symptom; urinary infection; alcoholism, smoking, or drug addiction; lesions and alteration in cutaneous sensitivity in the place where the electrotherapy will be applied; cognitive deficits; drug and/or physiotherapeutic treatment for UUI or current OAB; having any neurological disease; being in the gestational or puerperium period.

The presence of any signs of skin irritation that may be associated with electrostimulation will be considered as the criterion to discontinue the treatment. No concomitant care and interventions will be encouraged or prohibited during the study.

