### Minimizing missing data

In order to avoid and minimize missing data, all participants receive paper reminders with the date and time of each session. The investigator also makes phone calls to reinforce the scheduling of sessions. For data from the 24 h-VD, participants are given reminders in previous sessions so that they will not forget to complete the diary. Regarding the follow-up, the blinded evaluator contacts the participant by telephone about 3 days before the scheduled date, in order to arrange the best time and date for the assessment to be performed. As a way of monitoring adherence to treatment, the attendance records will be registries in the Session Monitoring sheets. In cases of dropout or withdrawal from the study, the data will be analyzed by intention-to-treat analysis. Participants that leave the study without performing the 12 proposed sessions (due to sickness, moving to another town, inability to attend sessions) will be considered protocol deviations.

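### Leakage outcomes are compared in all randomised women without using baseline leakage, although women who do not leak are eligible; this dilutes the secondary incontinence estimate and costs some power

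*Protocol article*

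**What the plan says.** All of this is in the protocol article.

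- **Entry (Participants and settings).** Women must be "with urgency, self-reported and confirmed by a score greater than or equal to 8" on the OAB-V8. The only exclusion by type of incontinence is "stress urinary incontinence with no urgency symptom". Nothing requires leakage.
- **Condition (Introduction).** Overactive bladder is described as "symptoms of urgency with or without UI".
- **Outcome (Measurement of results, primary and secondary outcomes).** One secondary outcome is "urinary incontinence (number of episodes of urinary loss Session Monitoring and Follow-up sheets and ICIQ-OAB, severity of UI (ICIQ-OAB". The text does not say whether severity means the questionnaire total or its single leakage item.
- **Score (Evaluation tools).** The only ICIQ-OAB score described is the 0-16 sum of items 3a (frequency), 4a (nocturia), 5a (urgency) and 6a (urgency incontinence).
- **Analysis (Statistical analysis plan).** "The comparison of urgency, voiding habits, UI, and quality of life between groups (TTNS, PTES, and placebo) and between stages" is done by repeated-measures ANOVA, or by an unnamed non-parametric test if residuals are not normal. Incontinence is handled exactly as urgency is. Baseline leakage is not used as a restriction, stratum or covariate.
- **Analysis set (Minimizing missing data).** "In cases of dropout or withdrawal from the study, the data will be analyzed by intention-to-treat analysis".

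**The concern.** A woman with urgency who does not leak is eligible in any arm. On a count of loss episodes, or on item 6a, she starts at the lowest possible value. She can get worse but has no leakage to lose, and the stated analysis cannot tell her from a leaking woman who did not respond.

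Two things follow for these measures. The average treatment difference shrinks in proportion to the share of women who leak. The mixture of women at the floor and women who change also adds between-woman variance that a variable recorded before randomisation could explain. A technique that helps leaking women could therefore show a small, non-significant incontinence result. Because groups are also compared at each stage, a chance difference between arms in the share who leak would feed into the reported difference.

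**Working it through.** **1. The plan's own figure.** Sample size gives f = 0.15, 5% significance, 90% power, 3 groups, 4 stages and N = 99. Assume a within-between interaction with correlation 0.5 and sphericity (neither is stated). Then the noncentrality is 0.15² × 99 × 4 / (1 − 0.5) = 17.82, with 6 and 288 degrees of freedom, and power is 90.0%. So 99 reproduces. No outcome is attached to f, so the calculation makes no allowance for women at the floor on leakage.

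**2. Dilution.** Let w be the share of women who leak at baseline (not in the documents; assumed 0.9, 0.7, 0.5). Let d be the treatment difference in change among leaking women, and let dry women change by 0 in both arms. The all-women difference is w × d, that is 90%, 70% or 50% of d.

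**3. Power for one active arm against placebo, 33 per arm, two-sided 5%.** Assume a change SD of 1 in leaking women and a placebo mean change m0 in leaking women; the active mean change is m1 = m0 + d.

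- All women: variance in each arm v = w + w(1 − w)m²; power = Φ(w·d / √((v0 + v1)/33) − 1.96).
- Wet-only: power = Φ(d / √(2/(33w)) − 1.96).

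Example with w = 0.5, m0 = 0.5 and d set for 80% wet-only power:
- d = 2.802 × √(2/16.5) = 0.975
- v0 = 0.5 + 0.25 × 0.25 = 0.5625
- v1 = 0.5 + 0.25 × 1.475² = 1.044
- standard error = √(1.6065/33) = 0.221
- 0.4875/0.221 = 2.21, and Φ(0.25) = 60%

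| Effect d (SD) | Placebo change m0 (SD) | All women, 10/30/50% dry | Wet-only, 10/30/50% dry |
|---|---|---|---|
| 0.5 | 0 | 48 / 39 / 29% | 49 / 40 / 30% |
| 0.7 | 0 | 76 / 63 / 48% | 77 / 66 / 52% |
| 0.7 | 0.5 | 74 / 57 / 39% | 77 / 66 / 52% |
| 0.73 / 0.82 / 0.98 | 0 | 79 / 76 / 71% | 80 / 80 / 80% |
| 0.73 / 0.82 / 0.98 | 0.5 | 77 / 69 / 60% | 80 / 80 / 80% |
| 0.73 / 0.82 / 0.98 | 1.0 | 73 / 59 / 47% | 80 / 80 / 80% |

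In the last three rows d is re-set at each w to give 80% wet-only power. It therefore grows as w falls, which widens the gap. A simulation of the fifth row (5,000 runs) gave 75/69/60% for all women.

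**4. What cannot be recovered.** Apply the dilution to the interaction model of step 1, using f√w and so ignoring the mixture variance. Power falls from 90% to 81/72/57% at w = 0.80/0.67/0.50, and wet-only gives the same 81/72/57%. At w = 0.33 it is 39% for all women and 37% wet-only. This part of the loss comes from having fewer informative women.

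**5. Adjusting instead of restricting.** With leakage status as a covariate and all women kept, simulated power (3,000 runs, assumptions of the fifth row) was 79/77/75%, against 79/78/76% wet-only. The covariate recovers nearly all that restriction does.

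**6. Levels rather than change.** Table 1 starts the monitoring cards at session 1, so they have no pretreatment value. The formula still applies with each arm's mean level among leaking women as m. For w = 0.7, d = 0.824, placebo level 1 SD above zero and active level 0.176: v0 = 0.7 + 0.21 = 0.91; v1 = 0.7 + 0.21 × 0.176² = 0.706; 0.577/√(1.616/33) = 2.61; power is 74%, against 80% wet-only.

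**7. Imbalance.** The chance SD of the between-arm difference in wet share is √(2w(1 − w)/33): 11 percentage points at w = 0.7 and 12 at w = 0.5.

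**The case against.** **A dry woman is not stuck at zero on everything.** A reader might infer that she can never show improvement on the incontinence outcomes. The document does not support that. On the 0-16 ICIQ-OAB total, the only score it describes, she can improve through frequency, nocturia or urgency, and on any leakage measure she can get worse. This stands; the point is confined to loss episodes and item 6a.

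**The all-women estimate is legitimate.** The trial studies women with urgency, and a smaller average effect in that population is not bias. Chance imbalance in the share who leak is already within the 5% error rate. Both stand, and they are reasons not to replace the all-randomised analysis with a wet-only one. They are no reason to leave a strong baseline predictor unused.

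**The power gap depends on assumptions.** With no placebo change and a moderate effect it is small, and in the interaction model it vanishes. This stands, so the size is given as a range. The planned post hoc contrasts are closer to the two-arm model, where the gap never favours ignoring baseline leakage.

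**Short recall windows.** Each card covers only the day before and the day of the session, so leaking women also record zeros. That stands: item 6a will not explain every zero.

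**The full plan may cover this.** Covariates for secondary outcomes are often left to it. But the article has its own analysis section, states that its purpose is to describe the statistical analysis, and fixes the same comparison for incontinence as for urgency.

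**Conclusion.** The point holds in limited form. Leakage is not required at entry, and the leakage outcomes are compared in all women without regard to who leaked at baseline. For loss episodes, and for severity if item 6a measures it, the between-group difference is about w times the difference among leaking women.

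The power cost against a wet-only analysis, for 10-50% dry, runs from about 1-4 points (no placebo change, effect 0.5-0.7 SD) to 20 points or more (half dry, placebo change 0.5-1.0 SD, effect near 1 SD). It rests on an assumed dry fraction, placebo change and effect, and on dry women staying dry.

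It would be wrong to conclude that N = 99 is undermined or that the OAB-V8 result is affected. The sample size names no leakage outcome, and the primary outcome concerns urgency, which every participant has. This is a minor, inexpensive improvement to a secondary analysis.

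**What to change.** In the Statistical analysis plan section, for loss episodes and incontinence severity only:

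1. Keep all randomised women and add pre-randomisation leakage (item 6a above 0) as a covariate. In the repeated-measures model include its interaction with stage, since the main effect alone does not explain differences in change.
2. Prespecify the treatment estimate, with confidence interval, in women who leak at baseline. Report new leakage in women dry at baseline descriptively, and the share leaking at baseline by group.
3. State that severity of incontinence is item 6a, not the 0-16 total, so that a change in frequency, nocturia or urgency is not reported as a change in incontinence.

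The cost is a few sentences and one added analysis of a secondary outcome. Item 6a is already collected before randomisation, so comparability within the leaking subset is kept. The wet-only estimate has a smaller denominator and applies only to women who leak. Trial status says no analysis had been performed, so on the article's account this could still be prespecified.
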